**Method:**

For Phase I, a convenience sample of ~50 adolescents will be recruited. These participants will have their PAEE assessed in three different modes of commuting. Regarding phase II, a total of 300 adolescents from different schools in three Spanish cities will participate in this cluster randomized controlled trial. As many schools as necessary to meet the target sample will be included. In addition, each school will be randomized as either an intervention or control group. Participants from intervention schools will be asked to complete a school-based cycling intervention, while participants from control schools will be asked to continue their same habits for 8 weeks. The school-based cycling intervention will last for 8 weeks and will include *Bikeability* sessions, along with encouragement strategies to increase adherence to cycling to and from school.

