### Study design and participants

2.1

The ENERGYCO study is a cluster randomized controlled trial to be conducted in high schools from three Spanish cities (Granada, Jaén, and Almería), where the schools will be the units of randomization, and individuals within the schools will be the units of analysis (participants). This project will consist of two main phases: Phase I will present a cross-sectional design which will take place before starting the Phase II. A cross-sectional approach will be adopted due to its suitability for capturing a snapshot of key variables of interest at a specific point in time, aligning with the objectives of this phase (i.e., comparing PAEE associated with different modes of commuting to school and developing predictive equations for measuring PAEE in Phase II). In contrast, for Phase II a cluster parallel-arm design will be employed to allocate interventions effectively to larger groups while accounting for potential intra-cluster variability, enhancing the external validity and generalizability of the results. The ENERGYCO study has been approved by the Review Committee for Research Involving Human Subjects at the University of Granada (Reference: 2496/CEIH/2021) and registered with a ClinicalTrials.gov ID: NCT06414668. In addition, the present study protocol has been written in accordance with the Standard Protocol Items: Recommendations for Interventional Trials (SPIRIT) statement (See Supplementary material 1).

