#### School recruitment and randomization

2.4.1

In Phase I, a convenience sample of approximately 50 students will be recruited. A call to action will be used to engage adolescents through the development of infographics and information about the aims of this phase, which will be disseminated through social media, personal contacts, or emails. Since these tests will be conducted outside the school timetable, no schools will be directly contacted. Instead, parents or legal guardians will be responsible for contacting the research team if their children are interested in participating in the study and they provide their consent. In this call to action, incentives, such as activity wristbands will be given away to participating adolescents. For Phase II, a specific selection protocol will be implemented through a random draw. A list of all public secondary schools in each of the participating cities of the government educational institutions in Andalucía will be obtained. The schools in the three cities (Granada, Almería, Jaén) will be contacted by phone, and if they are interested in participating, they will have to meet a series of inclusion and exclusion criteria presented in Table 1. During the call, a meeting will be arranged with interested schools to explain to the management team and teaching staff the main objective of the study, as well as to obtain official consent to participate in the project from the school. After that, the research staff with the help of Physical Education teachers will recruit participants and their families, by visiting selected classes and explaining the study to prospective adolescent participants and finally requesting the family’s consent. The inclusion and exclusion criteria for the participants are presented in Table 2. To complete the sample of students in the intervention group, several schools may be needed, as not all students will be able to participate in the school-based cycling intervention due to family reasons, distance, predisposition, etc. To encourage as many students as possible from the intervention school to participate (with their families’ consent) in the school-based cycling intervention, an incentive system will be planned similar to other studies (42, 43). This incentive will consist of a voucher to be redeemed for sports equipment, provided that the participant has completed the 8 weeks of intervention and presents valid data at both baseline and follow-up. Once finished the baseline assessment, the participating schools will be randomly assigned through a draw to either a control or experimental group.

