#### Sample size calculations

2.4.2

For Phase II, at least 250 participants are needed to ensure an acceptable sample size, assuming 5% precision (*α* err prob) and a very high statistical power of 95%. (Error 1-*β* err prob) (44). This calculation has been made considering a study objective where the effect of the intervention program on the different health variables of young people is evaluated (e.g., RMR, EE, PA levels, body composition, muscle strength). In this study there will be two main comparison groups (experimental group and control group) and for this the ANCOVA statistical analysis will be performed: fixed effects, main effects, and interactions (F test) and with an effect size = 0.25. It is assumed that there will be dropouts during the school-based cycling intervention (≈15% in the experimental group), so ≈300 adolescents will be recruited from different schools in the three Spanish cities. Following the forecasts in Figure 1, 100 adolescents would be needed in each city. The groups randomization will be done at a 1:1 ratio at city level (i.e., from each city, 50 participants will be randomized to intervention and 50 to control groups), as other studies have done before (45). Nevertheless, due to the low prevalence of cycling to school in Spain (46), we will try to recruit as many schools as necessary in each city to reach the number of 100 adolescents.

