##### Resting metabolic rate

2.7.1.1

RER will be measured using the Omnical metabolic cart (Maastricht Instruments, Maastricht, The Netherlands), a validated system for assessing volumes of oxygen consumption (VO_2_) and carbon dioxide production (VCO_2_) during resting conditions which a low measurement error for determining RER (1.7 ± 0.9%) (54). During the test, a ventilated plastic canopy will be connected to the instrument and placed over the participant, allowing the individual to breathe normally while the Omnical records CO_2_ and O_2_ levels in inhaled and exhaled air every 5 s. The device will be calibrated daily using a gas mixture of 18.0% O_2_ and 0.8% CO_2_. Data will be analyzed as the average VO_2_ (ml/min) and VCO_2_ (ml/min) over a 10-min stable period, aggregated by participant at baseline and follow-up. However, since the RMR measurement can only be performed at the research center in one of the participating cities, a contingency plan has been established in case participants from other cities cannot travel to the evaluation center. In such cases, the RMR will also be estimated for all participants using the Schmelze equation, which has demonstrated superior results compared to the gold standard among 12 equations, including a low measurement difference with the gold standard (−51.0 to 15.0 kcal/day), low % bias (−1.6 to 5.8%), an acceptable prediction percentage relative to the gold standard (40.7 to 59.0%), and a low RMSE (136.2 to 305.4 kcal/day) for adolescents with normal weight, overweight, or obesity (55).

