#### Statistical analysis

2.10.2

Descriptive analyses of all study variables presented with the mean (standard deviation) and frequencies (percentage) will be performed. Subsequently, the normality of the variables will be analyzed using histograms and normality tests. In Phase I, for the comparison of PAEE between the different modes of commuting (i.e., walking, cycling, and motorized-vehicle), a repeated measures ANOVA will be performed using the per-protocol approach. In addition, Student t-test or Mann–Whitney tests will be performed to compare the fluctuation of PAEE according to speed or distance commuted between active modes of commuting (i.e., walking vs. cycling).Within Phase II, the effects of the school-based cycling intervention on RMR and other health-related outcomes will be studied using an analysis of covariance (ANCOVA). Post-intervention RMR and other-health related values will be included as dependent variables, group (i.e., experimental group vs. control group) as fixed factor, and baseline outcome data as covariates. To evaluate the effect of the intervention on the secondary outcomes (i.e., physiological, physical, and psychosocial outcomes), we will conduct the same analysis used for the main outcomes (i.e., ANCOVA analysis using the intention-to-treat approach). Moreover, to control the variability between schools, the analyses will include adjustments for contextual and organizational variables, such as the SES of the school area, the length of cycling lanes, the availability of bicycle parking, and the level of engagement of teachers and students in the intervention. The estimates will be present as raw and standardized (z-scores; i.e., mean differences between follow-up and baseline data divided by the standard deviation), as an indication of the change the post-intervention z-scores will be calculated relative to the baseline mean and standard deviation. Effect sizes will be categorized as small (0.2 SDs), medium (0.5 SDs), and large (0.8 SDs), based on Cohen (93). Finally, to analyze the influence of covariates on the association between the intervention and the main outcomes (i.e., RMR and PAEE), mediation analyses will be performed. The intervention will be included as the independent variable, and the main outcomes as the dependent variables. Covariates included in the mediation analysis will encompass body composition, physical function, cognitive determinants, perceived barriers or autonomy, built-environment characteristics, weather, among others. In the statistical analysis, a value of *p* < 0.05 will be considered statistically significant.

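### Section 2.4.2 splits participants 50:50 within each city although whole schools are drawn, and the city level at which the 1:1 ratio is kept is absent from the stated ANCOVA

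*Protocol article*

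**What the plan says.** Three places make the school the unit of allocation. The abstract says "each school will be randomized as either an intervention or control group". Section 2.1 says "the schools will be the units of randomization". Section 2.4.1 says that, after baseline, "the participating schools will be randomly assigned through a draw to either a control or experimental group", and does not mention city in connection with that draw.

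Section 2.4.2 reads differently. It says "The groups randomization will be done at a 1:1 ratio at city level" and explains this as: "from each city, 50 participants will be randomized to intervention and 50 to control groups". The same section leaves the number of schools open, to be increased until each city reaches 100 adolescents. Table 1 sets only a minimum of eight consenting pupils per school.

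Section 2.10.2 gives the Phase II model: follow-up value as outcome, with "group (i.e., experimental group vs. control group) as fixed factor, and baseline outcome data as covariates". It then adds adjustment for school-level context, giving as examples the socioeconomic status of the area, cycling lanes, bicycle parking and engagement. City is not named.

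**The concern.** There are two linked problems.

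- **Unit.** Randomising 50 participants to each arm in a city and drawing whole schools are different procedures. If schools are drawn, the headcount per arm depends on school sizes and cannot be fixed at 50. If individuals were randomised, the trial would not be a cluster trial. A statistician preparing the draw cannot follow all these sections as written. The participant wording also invites an analysis that treats pupils as independently allocated.
- **Stratum.** If the ratio is kept 1:1 within city, city is a factor of the allocation. A model without it leaves between-city variation in the residual and offers no protection when the arms end up unevenly spread over cities.

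**Working it through.** **1. The plan's own recruitment figure.** 250 / (1 − 0.15) = 294.1, rounded up to 295, which fits the stated figure of about 300. Also 3 cities × 2 arms × 50 = 300. The headcount is consistent; the issue is how it is allocated.

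**2. Can a draw of schools give 50:50?** Fifty pupils per arm per city means anything from one school of 50 to about six schools at the Table 1 minimum (50 / 8 = 6.25). As an illustration with assumed sizes, take four schools in a city with 50, 25, 17 and 8 pupils (total 100). Allocating two schools to each arm allows only these splits:

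- 50 + 25 against 17 + 8: 75:25
- 50 + 17 against 25 + 8: 67:33
- 50 + 8 against 25 + 17: 58:42

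A 50:50 headcount would need one school against three. So 1:1 in schools and 1:1 in pupils are different rules, and the draw can guarantee only the first.

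**3. What leaving city out costs in the planned pupil-level ANCOVA.** The documents give no variance components. Assume that cities account for 2% or 5% of the variance remaining after baseline adjustment. The residual SD, and with it the standard error, is then inflated by at most:

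- 5%: √(1 / 0.95) = 1.026
- 2%: √(1 / 0.98) = 1.010

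That is about 1-3%.

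**4. What it costs in an analysis that respects schools.** Assume 12 schools of 25, so four per city and two per arm per city. Scale the total variance to 1, so that v_e = 1 − v_city − v_school, and let w = v_school + v_e / 25 be the variance of a school mean within city. Without city, the expected residual mean square on 10 df is [2(4·v_city + w) + 8w] / 10 = w + 0.8·v_city. With city it is w, on 8 df. The SE ratio is √(1 + 0.8·v_city / w).

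| v_city | v_school | w | SE ratio |
|---|---|---|---|
| 0.05 | 0.02 | 0.0572 | 1.30 |
| 0.05 | 0.05 | 0.0860 | 1.21 |
| 0.02 | 0.02 | 0.0584 | 1.13 |
| 0.02 | 0.05 | 0.0872 | 1.09 |

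Moving from 10 to 8 df raises the critical t from 2.228 to 2.306, a factor of 1.035. The ratios of interval width are therefore about 1.26, 1.17, 1.09 and 1.05.

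**5. Is city a substitute for handling schools?** Null trials were simulated with pupil-level models and 50 pupils per arm per city, with a city SD of 0, or of 0.3 against a within-city SD of 1. Baseline was not modelled. With no school effect, 50 pupils per school and a city SD of 0.3, type I error was 4.5% without city and 5.2% with it. With an assumed school ICC of 0.02 it was about 6% at 10 pupils per school, 10-12% at 25 and 16-17% at 50, whether or not city was in the model. City is a precision term; it does not repair ignored clustering.

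**The case against.** The strongest reply is that section 2.4.2 is loosely worded. Three other places say clearly that schools are randomised, the sentence opens with the ratio at city level, and its context is recruitment targets. Figure 1, which presents the process, is not available in the text reviewed. That reading is plausible and is the one the fix adopts. The sentence as printed still conflicts with the rest.

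The second reply is that the adjustment list is introduced by examples and so is open, that no section calls the draw stratified, and that a separate analysis plan may add city. In part this stands: the article does not exclude city. But it does not leave the model unstated either. It names the terms, and the examples are school-context descriptors, not allocation factors.

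Third, the gain is small in the analysis actually described. That stands: the larger figures belong to a school-respecting analysis that the article does not specify.

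Two stronger readings are tempting.

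- **RMR is measured differently by city.** A reader might infer this because "the RMR measurement can only be performed at the research center in one of the participating cities". Section 2.7.1.1 does not support it. The prediction equation is a contingency for participants unable to travel, and in that case it would be computed for everyone. The route follows ability to travel, may be mixed within a city, and would not be isolated by a three-level city factor.
- **Omitting city biases the effect estimate.** Schools are drawn at random, so unequal sizes give chance imbalance, some of which the baseline covariate would absorb. Imbalance could also arise after exclusions. The per-protocol analysis in section 2.10.1 drops intervention pupils who cycled too little and requires valid data at both times, and section 2.4.2 expects about 15% dropout in the experimental arm. That is a reason for protection, not evidence of a systematic bias.

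**Conclusion.** The point holds in two parts. First, section 2.4.2 conflicts with the abstract and sections 2.1 and 2.4.1 on what is randomised, and 50:50 by participant cannot be guaranteed by a draw of schools. This part needs no assumption. Second, city, the level at which the 1:1 ratio is kept, is missing from the stated ANCOVA.

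The size of the second part is modest and rests on assumed city shares of 2-5% after baseline adjustment. It is about 1-3% of the SE in the planned pupil-level model, and about 9-30% (5-26% in interval width after the lost df) in an analysis that respects schools, under the further assumptions of 12 schools of 25 and a school share of 2-5%. It is worth correcting because it is cheap; it does not undermine the trial.

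**What to change.** - In section 2.4.2, replace the participant wording with a statement that, within each city, schools are allocated 1:1 in a draw stratified by city, aiming for about 50 participants per arm per city. Describe the same stratified draw in section 2.4.1.
- In section 2.10.2, add city (three levels) as a fixed factor in every Phase II model, alongside a method that accounts for clustering by school (a school random effect or another cluster-robust method), not in place of it.

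**Cost.** The allocation wording and one model term change; city is already known for every school, and the target of 300 is unchanged. The 50:50 split becomes a target and not a guarantee. City uses 2 degrees of freedom. That is minor with 12 schools (10 to 8 at school level) but more noticeable with few schools: with six schools of 50 it would be 4 to 2.

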### Description and rationale of the ENERGYCO study

2.5

In Phase I the PAEE of different modes of commuting will be quantified by analyzing each participant individually in different controlled environments. For phase II, after recruiting schools and participants, an eight-week school-based cycling intervention will be implemented. The choice of an eight-week duration was based on the results reported in the systematic review by Dorothea et al. (47) on the effects of cycling interventions in a school setting. For example, although interventions lasting longer than 8 weeks demonstrate positive changes in physical fitness (43, 48), they also exhibit lower adherence, with a higher dropout rate among participants post-intervention. Therefore, considering that interventions lasting 4 to 8 weeks show effects on self-efficacy (49) or PA levels (50) and report a lower dropout rate, an eight-week duration was chosen for the school-based cycling intervention. The intervention will consist of adolescents having to cycle to and school for eight consecutive weeks. To encourage participants to complete the intervention, they will take part in a *Bikeability* training and different encouragement strategies will also be used during this period. Moreover, the ENERGYCO school-based cycling intervention shows relevant factors described in the current National Education Law for the curriculum of Compulsory Secondary Education. This approach is based on strategies proposed by the Active Living by Design Community Action Model (51), which involves preparing through the development of interventions, promoting education, and motivating students to cycle anywhere, as well as organizing activities with incentives and programs to engage participants. Regarding the control groups, participants in these schools will be asked to continue their daily habits. In addition, at the end of the eight-week cycling intervention in schools, control schools will be given the opportunity to conduct the *Bikeability* sessions and will receive all the motivational strategies used for the participating adolescents.

### Measurement procedures and outcome measures

2.6

#### Study assessment protocol

2.6.1

In Phase I, participants will perform three different simulations (i.e., commute by motorized-vehicle, walking, and cycling [see Figure 2]): (1) a simulation of driving to school will be performed by motorized-vehicle. After all the calibration process of the Cosmed K5 (both, flow and gas analyzers will be calibrated before every gas exchange measurement), a face-mask attached to the K5 will be place and gas exchange will be check during a two-minute period before the measurement start. After the check phase, gas exchange recording start during a five-minute period, while participants remain seated. Then, the participants will simulate commute in a motorized-vehicle by remaining seated in a chair for another 15-minute period, having previously walked for 2 mins simulating that participants are moving toward the motorized-vehicle from home. After this first simulation, there will be a five-minute period of cooling down. The total time of this first test will be 27 min. (2) A simulation walking to school will be conducted in a closed circuit defined by the research staff. The same procedures mentioned before will be followed. Then, the participant will walk for 15 min (the participant will determine the speed and intensity of walking) and finish with a five-minute cool down; (3) Participants will simulate a cycling route. They will wait for five-minute after walking and they will start cycling during 15-minute period along the designated route. The simulation will finish with a five-minute cool down period. The total time used in the walking and cycling simulations will be 45 min. These times were chosen because an average walking speed of 4.4–4.6 km/h would not exceed the distance Spanish adolescents are willing to walk to their educational center (1,350 m) (52). While no study in Spanish adolescents indicates the distance, they are willing to cycle to school, we estimated a distance of 4,200 m, the threshold distance used for Australian adolescents (53), with which a speed of approximately 15 km/h would not exceed 15 min. Detailed visual information on the evaluation and calibration process of the Cosmed K5 (Cosmed, Rome, Italy) can be found at the following link.^1^ In order that one active mode of commuting (e.g., walking) does not affect the post exercise oxygen consumption, thus PAEE, of the subsequent active mode of commuting (e.g., cycling), participants will alternate randomly by first performing the simulation of walking or cycling. In addition, the alternation of starting on the bike and walking will be counterbalanced by having the same number of participants starting on the bike or walking. Finally, all data will be downloaded using PC OMNIA.9 software v3.30.79 (Cosmed, Rome, Italy).

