##### Energy expenditure related to active commuting to school

2.7.1.2

PAEE related to different modes of commuting to school (i.e., walking, cycling, passive modes) will be measured using the Cosmed K5 portable metabolic system in Phase I. The Cosmed K5 has previously shown a good level of agreement compared to stationary metabolic carts at low cycling intensity (5.8% difference in VO_2_). At moderate intensities, it slightly underestimated VO_2_, VCO_2_, and energy expenditure (~6.6–6.9%). Additionally, during walking tests, the Cosmed K5 demonstrated high reproducibility, with a coefficient of variation of 4.5% for energy expenditure per kilometer and a concordance coefficient of 0.91. VO_2_ measurements were consistent, with low variability in the fraction of expired oxygen (coefficient of variation of 0.9%) (56). The Cosmed K5 is worn on the back with a harness and measures oxygen consumption (VO_2_) and carbon dioxide production (VCO_2_) in breath-by-breath mode. Before each assessment, the device will be calibrated using a reference gas mixture of 15.92% O_2_ and 5.03% CO_2_. Delay calibration for the breath-by-breath mode will also be performed (57). During the test, participants will breathe normally while commuting, and the Cosmed K5 will record data continuously. Data will be analyzed as the mean VO_2_ and VCO_2_ (ml/min) during each commuting mode. In Phase II, PAEE related to cycling will be estimated using predictive equations developed in Phase I. These equations will incorporate variables such as distance, speed, and heart rate, and will be cross-validated against PAEE measurements obtained with the Cosmed K5 to ensure accuracy. Therefore, data will be analyzed as the mean VO_2_ and VCO_2_ (ml/min) during each cycling trip to and from school, aggregated by participant during the intervention period.

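### Phase I: counterbalancing the walking and cycling bouts balances carry-over but does not prevent it, so half of any residual stays in each active mode's mean PAEE

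*Protocol article*

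**What the plan says.** Section 2.6.1 describes three simulations per participant. The vehicle simulation comes first; walking and cycling follow in random order. The stated purpose of the random order is that "one active mode of commuting (e.g., walking) does not affect the post exercise oxygen consumption, thus PAEE, of the subsequent active mode of commuting", and the order is "counterbalanced by having the same number of participants starting on the bike or walking". Some recovery is built in: there is a cool-down after walking, and for the next bout "They will wait for five-minute after walking and they will start cycling during 15-minute period along the designated route". On the total length the section says: "The total time used in the walking and cycling simulations will be 45 min".

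Section 2.7.1.2 averages oxygen uptake and carbon dioxide output over each mode. Section 2.10.2 compares the three modes by repeated measures ANOVA. Section 2.1 gives Phase I two aims: "comparing PAEE associated with different modes of commuting to school and developing predictive equations for measuring PAEE in Phase II". Section 2.7.1.2 then applies those equations to the cycling trips of Phase II, where energy expenditure is a primary outcome.

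**The concern.** The article itself names post-exercise oxygen consumption as the threat and offers order balance as the protection. Order balance protects one thing, the difference between walking and cycling, and only if carry-over is the same in both directions. It does not protect the level of either mode.

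Both Phase I aims use levels. The vehicle simulation always comes first and receives nothing from the active bouts, so carry-over does not cancel from walking versus vehicle or cycling versus vehicle. The cycling equation is meant for stand-alone trips in Phase II, while about half of its calibration recordings would come from participants who had just walked. Cross-validation against K5 recordings of the same kind would not reveal a shift that those recordings share.

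**Working it through.** **Inputs.** About 50 participants (2.2, 2.4.1) and equal orders (2.6.1), so 25 per order. No carry-over size is given, so every carry-over value below is an assumption.

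**The plan's own times.** Vehicle test: 5 + 2 + 15 + 5 = 27 min, as stated. Walking plus cycling: 5 + 15 + 5 + 15 + 5 = 45 min (5-min gap between bouts) or 15 + 5 + 5 + 15 + 5 = 45 min (10-min gap). Both reproduce the stated total, so both gaps are used below.

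**Bias of the pooled means.** Let cC be the carry-over of walking into cycling and cW that of cycling into walking.
- Cycling mean, and cycling minus vehicle: (25 × 0 + 25 × cC)/50 = cC/2.
- Walking mean, and walking minus vehicle: cW/2.
- Cycling minus walking: (cC − cW)/2, which is zero if carry-over is equal.

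A simulation (25 per order, 4,000 runs) agrees. With cC = cW = 2 units the biases are 0.99 (cycling), 0.99 (walking) and 0.00 (difference). With cC = 1 and cW = 4 they are 0.50, 2.01 and −1.51. First-bout means are within 0.01 of the truth in both cases.

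**Percentage scale (assumed).** Second-bout PAEE raised by 0%, 2%, 5% or 10% lifts the mode mean by 0%, 1%, 2.5% or 5%.

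**How large might it be?** Assume that excess oxygen uptake decays exponentially with time constant τ. The share of the preceding bout's end-exercise excess left in the pooled 15-min mean is ½ × exp(−gap/τ) × (τ/15) × [1 − exp(−15/τ)].

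| τ (min) | gap 5 min | gap 10 min |
|---|---|---|
| 1 | 0.02% | <0.01% |
| 2 | 0.5% | 0.05% |
| 5 | 5.8% | 2.1% |
| 10 | 15.7% | 9.5% |
| 15 | 22.6% | 16.2% |

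The range runs from practically nothing to material, and the article does not say where in it the trial lies.

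**What a period term does** (second active bout or not, first bout as reference). It estimates (cC + cW)/2 and removes half of that from each active mode's mean. The bias of the cycling level becomes cC/2 − (cC + cW)/4 = (cC − cW)/4. The walking-cycling bias stays (cC − cW)/2. Simulation (20,000 runs, SD units):

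| cC, cW | Quantity | no term | with term |
|---|---|---|---|
| 0.4, 0.4 | cycling mean | 0.200 | −0.001 |
| 0.4, 0.4 | cycling − vehicle | 0.201 | 0.001 |
| 0.2, 0.6 | cycling mean | 0.100 | −0.098 |
| 0.2, 0.6 | cycling − walking | −0.199 | −0.199 |

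With carry-over in both directions, the term shrinks the cycling-level bias only if cW < 3cC. In the unequal example the first-bout cycling mean has bias 0.001.

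**Precision.** Let k be the period effect in SDs of the within-person walking-cycling difference. Leaving it out inflates that contrast's SE by √(1 + k²): 1.005 at k = 0.1, 1.044 at 0.3 and 1.221 at 0.7. Including it costs one df (t critical value 2.0096 on 49 df, 2.0106 on 48). The first-bout analysis has an SE ratio of √(50/25) = 1.414.

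**The case against.** The strongest reply is that no harm is shown. Participants walk at their own pace and then have a cool-down and a wait; with fast recovery the residual is well under 1% of the preceding excess. Randomised, balanced order is a standard response to order effects, and the sentence states a purpose, not a proof. All of this stands and limits the weight of the point, but it does not make the sentence right: whatever protection the levels have comes from recovery time, not from order balance.

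A second reply is that an order term and first-bout fits are details that an article may leave to the full plan. That also stands. Their absence is not the finding; they are offered as the cheap way to act on it.

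A reader might infer that the recovery interval is too short or badly specified. The document does not support that. The 45-min total fits more than one gap, calibration before each measurement may add time, and Figure 2, which is not shown here, may settle the schedule.

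A reader might also infer that the Phase II comparison is compromised. That is not supported either. Transfer into the equation is possible, not certain, because heart rate is a predictor and may absorb part of it. A purely proportional shift would change raw PAEE but not p-values or standardised effects, and RMR is untouched.

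**Conclusion.** The point holds as a minor one. Section 2.6.1 credits counterbalancing with preventing an effect that it only balances. At equal orders exactly half of any residual remains in each active mode's mean and in its contrast with the vehicle simulation, and the cycling equation may inherit it. The one-half is algebra and needs only the equal orders; the size of the residual is unknown and may be nil.

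Two further readings go too far. One is that the walking-cycling comparison is biased: that requires carry-over to differ by direction, which the article neither shows nor rules out. The other is that a period term would clean the mode levels: it does so only when carry-over is equal, and at cC = 0.2 and cW = 0.6 it merely turns +0.10 SD into −0.10 SD. Its dependable gain is precision in the walking-cycling contrast. Only the first-bout recordings are free of walking-cycling carry-over whatever its direction.

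**What to change.** 1. In 2.6.1, say that random, counterbalanced order balances carry-over between walking and cycling rather than preventing it.
2. In 2.10.2, add a period term (first or second active bout) to the Phase I mode comparison. The balanced walking-cycling estimate does not change, the period effect leaves its SE, and the cost is one df. Do not present the term as a correction of mode levels.
3. As a sensitivity analysis, refit or check the cycling equation, and repeat the active-versus-vehicle contrasts, on first-bout recordings only. Because the order is randomised, these are a random half of the sample. The cost is precision: about 25 recordings per mode, with the SE of a mode mean about 1.41 times larger.

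No new data or change of procedure is needed.
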